### Statistical analysis

All assessments will be completed using an online format, with data stored online on a secure server accessible by the researchers only. Data entry is completed by participants online and responses are restricted to a predetermined range. The data analyst will be blinded to the condition of participants. Analyses will be on an intention-to-treat basis (i.e., include all randomised participants that complete two or more time-points in the linear mixed models analysis, regardless of the dose of c-MeST or usual care received), with supplementary per protocol analyses (i.e., analysis of participants that have completed all time-points). Linear mixed models will be conducted to assess differences between conditions on the primary and secondary outcomes at each time-point relative to baseline. This statistical method will facilitate inclusion of participants with missing data using a full-information ML estimator. Condition will be modelled as a fixed effect. Time will be modelled as a random effect, grouped within participants. If the groups differ in how much treatment they received in usual care during their participation in the trial, this will be used as a covariate in analyses.

To test mediation effects, primarily whether the effects of group on depressive symptoms over time is mediated through changes in AMT scores over time, analyses will be conducted using a bias-corrected bootstrap test. Power calculations indicate that the sample size will provide power of 0.80 to detect significant indirect effects given small-to-moderate effect sizes between group and depression change, and small-to-moderate effect sizes between changes in AMT scores and depressive symptoms [45]. Given the small number of sites anticipated to be used for recruitment into the present study, site will be dummy coded and included as a covariate in all analyses to adjust for potential between-site differences in outcomes.

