### Primary outcomes

The primary outcomes of the study will be the proportion of participants with a diagnostic status of MDE using the electronic Psychological Assessment Scale (e-PASS) [34] and change in mean self-report depressive symptoms using the shortened version of the depressive subscale from the Depression, Anxiety, and Stress Scale (DASS) [35]. Autobiographical memory specificity will be assessed at all time-points using the standard ten-item Autobiographical Memory Test (AMT), with five positive and five negative cue words [36]. We are primarily interested in the changes in outcome measures between baseline and 3 months.

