### Power calculation

Using G*Power V.3.1 [44], it was calculated that a total sample of 128 participants will be needed. This will be sufficient to detect a moderate-sized, clinically meaningful between-groups effect of *d* = 0.50, with 0.80 power and alpha level of 0.05 (two-tailed), while controlling for amount of usual care treatment (type and amount monitored at each time-point). We will aim to recruit 154 participants at baseline to allow for 20% attrition.

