### Procedure

Eligible help-seeking youth reporting depressive symptoms will be identified by trained mental health workers through normal intake procedures at participating services. Exclusion criteria of psychotic, neurodevelopmental and substance use disorders will also be assessed at this point. The youth will be informed of the study and asked for permission to be followed up by a member of the research team and invited to participate. They will then be sent an online link with a plain language statement to read (Additional file 2). Consent to participate will be given by clicking an arrow to take them to the next page at the end of the plain language statement to advise of this. They will then complete screening questions to verify eligibility. If participants are eligible, they will be randomised to one of the two conditions (c-MeST and usual care *or* wait-list c-MeST (to be offered in 6 months) and usual care) using computer-generated simple randomisation following completion of the baseline questionnaire. The researchers will be blinded to this process. Participants randomised to c-MeST and usual care will have immediate access to the online c-MeST program and complete online questionnaires at baseline, 1-, 3-, and 6-month time-points. All participation will be online and either involve accessing the memory intervention application or accessing surveys which will be completed via Qualtrics. Participants will receive automated prompts to complete survey measures at each time point. During the first month of access to the intervention, participants will be prompted with automated reminders every second day to engage in the modules. Participants randomised to wait-list c-MeST and usual care condition will complete online questionnaires and receive access to the c-MeST program after the 6-month follow-up. Therefore, all participants will have received usual care and c-MeST by the cessation of the study. No adverse or serious harm is anticipated as part of the online intervention; however, participants will be able to access support through their usual care provided and a list of contact details for support services will also be provided to participants.

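### The set called intention-to-treat excludes every randomised participant who returns no follow-up survey, and the plan's own likelihood model does not need that exclusion

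*Protocol article*

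**What the plan says.** The Statistical analysis section states: "Analyses will be on an intention-to-treat basis". A parenthesis then defines the phrase: the analysis will "include all randomised participants that complete two or more time-points in the linear mixed models analysis", whatever amount of c-MeST or usual care was received. The only supplementary set is narrower, being those who completed every time-point.

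The same section chooses linear mixed models to "assess differences between conditions on the primary and secondary outcomes at each time-point relative to baseline", and says of the method: "This statistical method will facilitate inclusion of participants with missing data using a full-information ML estimator".

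The Procedure section fixes the order of events. Eligible participants are randomised "using computer-generated simple randomisation following completion of the baseline questionnaire". The c-MeST arm will then "complete online questionnaires at baseline, 1-, 3-, and 6-month time-points", and the wait-list arm also completes online questionnaires before gaining access after the 6-month follow-up.

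The Primary outcomes section adds: "We are primarily interested in the changes in outcome measures between baseline and 3 months". The Power calculation section gives 128 as the number needed and 154 as the recruitment target, allowing for 20% attrition.

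**The concern.** Intention-to-treat means that all randomised participants are analysed in the arm to which they were assigned. Here membership depends on something that happens after randomisation, namely returning at least one follow-up survey. The clause about dose received protects against exclusion for poor adherence. It does not bring back people with no follow-up.

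The rule also works against the stated reason for the model. Baseline is one of the four modelled time-points, so a likelihood fit can keep a participant who has only a baseline score. Those scores are what allow the model to correct for loss that depends on baseline severity. Once they are removed, the change-from-baseline contrast compares two groups whose baseline means may have been moved apart by selective loss.

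At stake are an inaccurate label on the main analysis and a possible bias, of unknown direction, in the depressive-symptom result.

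**Working it through.** **1. The plan's own figures.** For d = 0.50, two-sided alpha 0.05 and 80% power, the exact t calculation gives 64 per arm, or 128 in total (power 0.801). This agrees with the plan. The target follows from 128 × 1.2 = 153.6, rounded to 154.

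**2. How many can be excluded.** 0.20 × 154 = 30.8, about 31, which would leave about 123. This is a ceiling: anyone who returns a single 1-, 3- or 6-month survey stays in.

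**3. Formula for the bias.** Work in baseline SD units with equal variances. Let r be the baseline to follow-up correlation, and D the mean baseline of retained c-MeST participants minus that of retained controls. In the retained set, the difference in mean change has expectation:

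true effect + (r − 1) × D

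Randomisation makes D zero in expectation over all randomised participants. If baseline-only participants are kept, the likelihood fit in effect moves each arm's follow-up mean back to its full baseline mean. The (r − 1) × D term then disappears.

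**4. Inputs that are assumptions, not in the documents.** True effect -0.50 SD (the plan's d, signed so that negative means benefit); r of 0.3, 0.5 and 0.7; standard normal baseline; logistic loss with a given slope per baseline SD; all loss being of people with no follow-up at all.

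**5. Largest case considered.** Loss is 29% in c-MeST with slope +0.7, and 12% in control with slope 0 (average 20.5%). Numerical integration gives a retained baseline mean of -0.185 in c-MeST and 0 in control, so D = -0.185.

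| r | (r − 1) × D | Retained set | Retained set, slope reversed | All randomised |
|---|---|---|---|---|
| 0.3 | -0.7 × -0.185 = +0.130 | -0.37 | -0.63 | -0.50 |
| 0.5 | -0.5 × -0.185 = +0.093 | -0.41 | -0.59 | -0.50 |
| 0.7 | -0.3 × -0.185 = +0.056 | -0.44 | -0.56 | -0.50 |

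**6. Milder and null cases, at r = 0.5.**
- Loss halved (15% and 6%), slopes 0.7 and 0: D = -0.099, bias +0.049, estimate -0.45.
- Loss 20% in both arms, slopes 0.7 and 0.35: D = -0.061, bias +0.031, estimate -0.47.
- Same slope 0.7 in both arms but loss 29% and 12%: D = -0.186 + 0.080 = -0.106, bias +0.053, estimate -0.45. A difference in rate alone is therefore enough once loss depends on baseline.
- Same slope and same rate, or no dependence on baseline: D = 0, bias 0.

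**7. Check at the trial's size.** Simulation with 154 participants, four time-points, a random-intercept maximum likelihood model, no true arm difference, r = 0.5, about 20% loss and 150 replicates. With slopes +0.8 and 0, the 3-month contrast averaged 0.06 SD under the two-time-point rule and -0.01 SD with all randomised (Monte Carlo standard error 0.014). Rejection was 5% and 6%.

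**The case against.** **Severity and size.** Much of the case against a severe reading stands. The 20% is general attrition, and those with no follow-up at all may be far fewer. The documents give no correlation, no arm-specific loss and no relation of loss to severity. In the trial-size check with dependence in one arm only, the false-positive rate stayed near 5%.

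**Differential loss is conjecture.** It is plausible, since only one arm has sessions to complete and the other waits for access. But survey prompts go to everyone, and the every-second-day reminders concern the modules.

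**Dependence on the model.** The bias arises because baseline is a modelled response. With baseline as a covariate, the same retained participants gave 0.00 SD bias under this mechanism. A condensed article may not give the full model. Still, the contrast it does state is relative to baseline, and it names no baseline-covariate model.

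**Stronger readings to avoid.** A reader might infer that the primary comparison will be biased, or that type I error is inflated. Rejection did reach 17%, against 5% with all randomised, when loss had opposite severity slopes in the two arms (+0.8 and -0.8; bias 0.17 SD). Nothing in the documents suggests that pattern. A reader might also fault the article for naming no multiple imputation or delta-adjusted analysis. Such details are commonly left to an analysis plan, so their absence is not a finding.

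None of this rescues the definition. The article states the set explicitly, and no section restores the excluded participants.

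**Conclusion.** The definition is wrong as written: a set chosen by a post-randomisation event is labelled intention-to-treat. That conclusion needs no assumption beyond the order of events in the Procedure section. At most about 31 of 154 participants are affected.

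The consequence for the estimate is conditional. Over the inputs considered, the bias runs from 0 to about 0.13 SD, in a direction that cannot be known in advance. The top of that range is 0.13 / 0.50 = 26% of the planned effect. It needs r = 0.3, a slope of 0.7 in one arm only, loss of 29% against 12%, and every lost participant missing all three follow-ups. The range illustrates these assumptions and is not a bound. The point is one that should be fixed; it does not show that the trial's result will be misleading.

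**What to change.** In the Statistical analysis section, delete the condition on two or more time-points. Define intention-to-treat as all randomised participants, analysed in the arm assigned. State that the likelihood model has baseline as a modelled time-point and is fitted to all of them, including those with baseline only. The present set can be kept under another name as a sensitivity set.

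The cost is one changed sentence. The baseline scores are already collected before randomisation. The change corrects loss that baseline explains; it does not correct loss driven by outcomes that were never observed.

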Without addressing low memory specificity or OGM, individuals are less likely to experience reductions in depressive symptoms during treatment [15]. Indeed, OGM is predictive of the course of depression, independent of severity [14]. Encouragingly though, memory specificity is demonstrably amenable to change with MeST. Previous research has indicated that youth find autobiographical memory-based interventions to be acceptable and effective [29]. The treatment is low-intensity for youth in the sense that it is not designed to be emotionally arousing, confronting or onerous. Given this, online c-MeST is an ideal candidate for an adjunct intervention that can be delivered alongside other treatments to specifically target this cognitive vulnerability. Enhancing the ability to retrieve specific memories may help to mitigate against maladaptive processes such as cognitive avoidance and rumination [30] and facilitate retrieval of previous experiences to aid in problem-solving [31]. Further, the ability to reappraise beliefs or experiences appears useful for reducing depressogenic thinking [32], and an improved ability to retrieve specific information from autobiographical memory may provide useful content to aid in this cognitive reappraisal. This study will examine the effect of c-MeST in addition to usual care (such as psychological and/or counselling support or medication prescribed for depression) and test whether it enhances treatment effects and reduces risk of depression at follow-up.

The aim of this study will be to conduct the first randomised controlled trial of c-MeST as an add-on intervention to usual care for young adults experiencing a major depressive episode (MDE). This design will allow us to assess whether adding c-MeST as an adjunct intervention to improve memory specificity enhances outcomes on depressive symptoms. We hypothesise that youth that engage in c-MeST, in addition to usual care, will report significantly lower rates of MDE and lower severity of depressive symptoms at follow-up time-points relative to a control group receiving only usual care. It is also hypothesised that the c-MeST group will report significantly greater changes in memory specificity at the follow-up time-points, and that changes in autobiographical memory specificity will predict changes in depressive symptoms.

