### Participants

The inclusion criteria will be: (i) 15–25 years, (ii) recent or current engagement with a mental health service provider (iii) residing in Australia, (iv) a current diagnosis of an MDE and (v) internet access. The exclusion criteria will be: (i) non-fluency in English and (ii) psychotic, neurodevelopmental and substance use disorders.

Regarding risk, if a participant scores ≥ 21 on the Suicidal Ideation Attributes Scale (the cutoff for risk of suicidal behaviour) then they will receive information regarding helplines/support they might wish to contact. Otherwise, duty of care for risk will be managed by usual risk management protocols through the service they are receiving to increase the generalisability of the findings, comorbid mental health disorders will not be an exclusion criterion of those listed above.

Usual care for participants will vary. As we are recruiting participants at the time of engagement with a mental health service they will be receiving evidence-based treatment for their depressive symptoms (such as anti-depressant medication or psychological/counselling support). Participants will be free to cease involvement in the study at any time.

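### The MDE analysis uses no baseline severity information: MDE status is essentially constant at entry, and the baseline DASS and AMT scores are not named as covariates

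*Protocol article*

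**What the plan says.** The Primary outcomes section of the protocol article names two primary outcomes, the proportion with MDE on the e-PASS and change in the DASS depression score, with main interest in baseline to 3 months. One model sentence in Statistical analysis covers them all: "Linear mixed models will be conducted to assess differences between conditions on the primary and secondary outcomes at each time-point relative to baseline".

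The same section names two covariates. One is unconditional: "site will be dummy coded and included as a covariate in all analyses to adjust for potential between-site differences in outcomes". The other, the amount of usual care received during the trial, enters only if the arms differ on it.

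Under Participants, an inclusion criterion is "iv) a current diagnosis of an MDE". The abstract places DASS at baseline and at every follow-up. For memory specificity, Primary outcomes says: "Autobiographical memory specificity will be assessed at all time-points using the standard ten-item Autobiographical Memory Test (AMT"). Under Procedure, randomisation follows completion of the baseline questionnaire, so both scores predate allocation. The Background also states that "OGM is predictive of the course of depression, independent of severity".

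**The concern.** A comparison relative to baseline helps precision when the baseline value varies between people and predicts the later value. For DASS it can do so. For MDE status the entry criterion makes the baseline value yes for essentially everyone, so it cannot explain who still has an MDE at 3 months. Neither named covariate is a baseline measure of illness severity. The model therefore takes baseline information into account for the continuous primary outcome and takes none for the binary one.

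At stake is precision. A yes/no outcome already carries less information than the score on which the sample was sized. The trial holds two graded pre-randomisation measures that could return part of that loss. The protocol itself describes the construct behind one of them as prognostic.

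**Working it through.** **Inputs from the protocol article (Power calculation).** Standardised mean difference d = 0.50, two-sided alpha 0.05, target power 0.80, and total N = 128: "it was calculated that a total sample of 128 participants will be needed".

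**Assumptions, because the documents give no figure.** Equal arms of 64. Control MDE rate at 3 months of 0.50, with a range of 0.30 to 0.70 (the Background says about half do not remit on first-line treatment). Latent correlation rho, between the baseline severity score and the severity underlying MDE status at follow-up, from 0 to 0.7.

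**1. The plan's own figure.** Two-sample t-test, noncentrality d × √(n/2) = 0.5 × √(64/2) = 2.83. Power is 0.801 at 64 per arm and 0.795 at 63, so 128 is reproduced. It includes no precision gain from covariates: an F-test at the same effect size with one to three covariates still gives 0.801.

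**2. What the baseline row adds for MDE.** If Y₀ = 1 for everyone, change is Yₜ − 1. Its variance equals that of Yₜ, and the arm difference in change equals the arm difference in follow-up status. In 300 simulated trials, the linear mixed model with the baseline row had power 0.55 for the 3-month contrast, and a plain two-group comparison at 3 months had 0.57. The baseline row brought no gain.

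**3. Power for MDE at the planned size.** Put d = 0.50 on a latent normal scale. The c-MeST rate is Φ(Φ⁻¹(0.50) − 0.50) = Φ(−0.50) = 0.309.
- Difference: 0.500 − 0.309 = 0.191.
- Pooled SE: √(2 × 0.4045 × 0.5955/64) = 0.0868.
- Unpooled SE: √((0.25 + 0.2135)/64) = 0.0851.
- Power: Φ((0.191 − 1.96 × 0.0868)/0.0851) ≈ 0.60.

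Over control rates of 0.30 to 0.70 this is 0.51 to 0.61. The logit conversion (odds ratio exp(0.5π/√3) = 2.48) gives 0.54 to 0.72. MDE is the weaker comparison under either conversion.

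**4. Gain from one baseline severity score.** Logistic regression, 64 per arm, 5,000 simulated trials per row, power without → with the score:

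| Latent rho | Control rate 0.50 | Control rate 0.70 |
|---|---|---|
| 0 | 0.61 → 0.61 | 0.60 → 0.59 |
| 0.3 | 0.61 → 0.62 | 0.61 → 0.63 |
| 0.4 | 0.61 → 0.65 | 0.61 → 0.65 |
| 0.5 | 0.61 → 0.68 | 0.62 → 0.67 |
| 0.6 | 0.60 → 0.70 | 0.61 → 0.70 |
| 0.7 | 0.61 → 0.76 | 0.61 → 0.75 |

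With no true effect, the adjusted test rejected in about 5% of trials.

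**5. Cross-check on the observed scale.** At a 50% rate, a latent correlation shrinks by φ(0)/√(0.5 × 0.5) = 0.399/0.5 ≈ 0.80 when measured against yes/no status, so latent 0.5 is about 0.40 observed. With the logit conversion (0.50 versus 0.288), an unpooled variance and the factor 1 − 0.40² = 0.84, power rises from 0.712 to 0.785. That is about 7 points, in line with the table.

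**6. How the covariate must enter.** In a mixed model that keeps the baseline row, a time-constant term γx is the same at baseline and at 3 months, so it cancels from the change-from-baseline contrast. In 200 simulated trials per setting (random intercept, control rate 0.50, latent d = 0.50):

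| Latent rho | No covariate | Main effect only | With covariate-by-time terms |
|---|---|---|---|
| 0.3 | 0.535 | 0.535 | 0.545 |
| 0.5 | 0.585 | 0.585 | 0.62 |

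**The case against.** The strongest case against is that nothing here is stated wrongly. A randomised comparison without severity adjustment is valid. One sentence covers all outcomes and does not claim that baseline MDE is informative. A condensed article may also leave prognostic covariates to a fuller plan. The point on validity stands: a reader might infer that chance imbalance in severity under simple randomisation biases the MDE result, but the standard error already allows for that variation. The point on leaving it to a fuller plan stands only in part, because the article does set out covariates, with site in every analysis, and baseline severity is not among them.

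A reader might also infer a gain of about 12 points. That figure comes from the variance factor at an observed-scale correlation of 0.5 (power 0.712 to 0.829), which needs a latent correlation of about 0.5/0.80 = 0.63. No document supports so high a value. Because everyone enters in an MDE, the spread of baseline DASS is probably narrowed, which makes it less likely still.

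Nor would adjustment rescue the MDE comparison. No value in the table in step 4 reaches 0.80. The larger cause of low power is that the sample was sized only for a mean difference, which is a separate matter. The added contribution of AMT beyond DASS has not been estimated; the Background sentence asserts that it is prognostic but gives no strength.

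Finally, adding a covariate to the model as worded would do nothing, as step 6 shows. That objection is right, and the fix allows for it.

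**Conclusion.** The point holds as one of efficiency, not validity. As published, the model uses essentially no baseline severity information for MDE status, although two suitable scores are collected before randomisation. At a 50% control rate and 64 per arm, one score is worth about 1 to 4 points of power at a latent correlation of 0.3 to 0.4, about 7 at 0.5 and about 10 at 0.6. At zero correlation nothing is gained and nothing material is lost.

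These sizes rest on an assumed control rate, an assumed correlation and the translation of d = 0.50 to the MDE scale. The instrument for the entry diagnosis is not named, so a few baseline e-PASS results might not be yes; that would not change the conclusion.

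**What to change.** In Statistical analysis, state that MDE status will be analysed at the post-baseline time-points only (1, 3 and 6 months, with main interest at 3 months). Name the baseline DASS depression score and the baseline AMT score as pre-specified continuous covariates, in addition to site. Report a covariate-standardised risk difference beside any odds ratio, so that the result still reads as a difference in the proportion with MDE.

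If the baseline row is kept, specify covariate-by-time terms; a main effect alone leaves the contrast unchanged.

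The cost is a few lines of wording and slightly more analysis work, with no new data. If a logistic model is used, its odds ratio is conditional on the covariates, which is why the standardised risk difference must accompany it.

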**Methods/design:**

Young people aged 15–25 years with a major depressive episode (MDE) will be recruited and randomised to have immediate access to the seven session online c-MeST program in addition to usual care, or to usual care and wait-list for c-MeST. The primary outcomes will be diagnostic status of an MDE and self-reported depressive symptoms assessed at baseline, 1-, 3- and 6-month intervals. Autobiographical memory specificity and other variables thought to contribute to the maintenance of reduced memory specificity and depression will be assessed as mediators of change.

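### The linear mixed model prescribed for every primary outcome does not suit yes/no MDE status, which is (almost) constant at baseline, so its standard errors and p-values are generally not at nominal level

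*Protocol article*

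**What the plan says.** All of this is in the protocol article.

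- Primary outcomes: the first is "the proportion of participants with a diagnostic status of MDE", measured with e-PASS. The second is "change in mean self-report depressive symptoms using the shortened version of the depressive subscale" of the DASS. The first is binary, the second a score.
- Abstract, Methods/design: "The primary outcomes will be diagnostic status of an MDE and self-reported depressive symptoms assessed at baseline, 1-, 3- and 6-month intervals".
- Participants: entry requires "a current diagnosis of an MDE".
- Primary outcomes, on timing: "We are primarily interested in the changes in outcome measures between baseline and 3 months".
- Statistical analysis: "Linear mixed models will be conducted to assess differences between conditions on the primary and secondary outcomes at each time-point relative to baseline". Condition is a fixed effect, time is a random effect within participants, and estimation is by full-information maximum likelihood so that participants with missing visits can be kept.

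No model for a binary outcome is named, and MDE status is not excepted from the linear model.

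**The concern.** The article does not leave the model for MDE status open. It names one model and one contrast for all primary outcomes, and for this outcome the model does not fit. A later analysis plan would either inherit the problem or contradict the published text.

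A standard linear mixed model assumes one residual variance across visits. For MDE status the variance is about 0 at baseline, because of the entry criterion, and p(1-p) at each follow-up, where p changes over time. The model averages these and applies the average to every visit. At stake are the interval and p-value for the first hypothesis in the Background, a lower rate of MDE in the c-MeST arm.

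**Working it through.** **The plan's own figure.** The article gives no MDE rates and no calculation for this outcome. Its total of 128 rests on d = 0.50, 80% power and two-sided alpha 0.05. A two-sample t-test gives 63.77, so 64 per arm and 128 in total. That figure reproduces, but it says nothing about MDE status. The MDE rates and correlations below are therefore assumptions.

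**Set-up.** Take a random-intercept linear mixed model with condition x categorical time, four visits, complete data and no treatment effect. Let S be the 4 x 4 covariance matrix of MDE status, with baseline row and column equal to 0.

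- Expected within-person mean square: MSW = (tr S - 1'S1/4)/3.
- Variance the model assigns to one person's change from baseline: 2 x MSW.
- True variance of that change at visit k: p_k(1-p_k), because baseline is constant.
- Ratio of model SE to true SE: R = sqrt(2 x MSW / [p_k(1-p_k)]).
- True type I error of a nominal 5% test: 2[1 - Φ(1.96R)].

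**Case 1: equal MDE rate at all follow-ups, common correlation r.** With v = p(1-p), tr S = 3v and 1'S1 = 3v + 6rv. So 2 x MSW = v(1.5 - r) and R = sqrt(1.5 - r).

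| r | R | type I error |
|---|---|---|
| 0.3 | 1.10 | 3.2% |
| 0.5 | 1.00 | 5.0% |
| 0.7 | 0.89 | 8.0% |

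**Case 2: 100/80/50/40% at 0/1/3/6 months.** Follow-up variances are 0.16, 0.25 and 0.24, so tr S = 0.65. Two binary variables with rates a > b cannot correlate above sqrt(b(1-a)/[a(1-b)]). For 80% and 40% the limit is sqrt(0.08/0.48) = 0.41, so a common r must stay at or below 0.41.

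- r = 0.1: 1'S1 = 0.778 and MSW = 0.152. At 3 months R = sqrt(0.304/0.25) = 1.10, type I error 3.1%. At 1 month R = sqrt(0.304/0.16) = 1.38, type I error 0.7%.
- r = 0.4: 1'S1 = 1.163 and MSW = 0.120. At 3 months R = 0.98, type I error 5.5%. At 1 month R = 1.22, type I error 1.6%.
- Each pair at its own maximum (nobody relapses): the covariances are 0.10, 0.08 and 0.20, so 1'S1 = 0.65 + 2 x 0.38 = 1.41 and MSW = 0.099. Type I error is 8.1% at 3 months (R = 0.89) and 2.9% at 1 month (R = 1.11).

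**Case 3: 100/70/60/50%.** The same formula gives 2.2% to 6.7% at 3 months for r = 0.1 to 0.6, and 9.6% if nobody relapses.

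**Does a random time effect cure it?** The article makes time random, so the closed form is not exactly its model. Simulation with 64 per arm, complete data, REML and 500 runs per setting gave R at 3 months of 0.95 to 1.17 with a random intercept and 0.90 to 1.13 with a random slope added. The implied type I error over both was 2.2% to 7.9%. Only 14 of 24 settings finished before a numerical failure, so this supports the closed form but is not a full survey.

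**Does changing the link suffice?** No. A logistic model that keeps the constant baseline row shows complete separation: time coefficients near -24 with SE about 16,400. With baseline dropped, a logistic comparison at 3 months (assumed 60% in both arms, 64 per arm) had simulated type I error 4.7%.

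**The case against.** Much can be said for the plan, and most of it stands as a limit on the point.

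- **The contrast is not meaningless.** A reader might infer that change from baseline has no meaning when everyone starts with an MDE. If baseline is 1 in both arms, the difference in change is the difference in follow-up proportions, a proper risk difference that is unbiased with complete data. The baseline reference is redundant for this outcome, no more.
- **The standard errors are not always wrong.** With equal follow-up rates they are right at r = 0.5, and in Case 2 the 3-month error is small near r = 0.4.
- **Large inflation needs attainable inputs.** A reader might put r = 0.5 or 0.7 into the 80/50/40% path and quote a 3-month error near 10%. Binary data with those rates cannot be so correlated.
- **The baseline rate may not be exactly 100%.** The Participants section does not say that e-PASS makes the entry diagnosis, and the Procedure section mentions only service intake and screening questions. The e-PASS rate at baseline may be slightly lower, which leaves nearly the same problem.
- **Fitted probabilities outside 0 to 1** matter little. With condition x categorical time and complete data the fitted means are the observed proportions. Values out of range arise with covariates or individual predictions.
- **Likelihood estimation was chosen for missing data,** and the article expects 20% attrition. A replacement should not give that up.

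None of this makes one residual variance right for an outcome with almost no variance at one visit and p(1-p) at the others.

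**Conclusion.** The concern holds as a misspecified model for one of two primary outcomes. The 3-month difference in proportions is unbiased with complete data; what is generally off nominal level is its standard error, confidence interval and p-value. In the attainable cases examined, type I error at 3 months runs from about 2% to 10% against a nominal 5%. At 1 month, in Case 2, the test is conservative throughout (0.7% to 2.9%). The direction at 3 months depends on follow-up MDE rates and within-person correlation, which the article does not give, so it cannot be known in advance.

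These sizes rest on assumed rates, equal arms, complete data and, for the closed form, a random intercept only. The documents do not support a claim that the treatment effect will be biased or that every p-value will be wrong. Important rather than critical.

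**What to change.** In the Statistical analysis section:

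1. Limit the linear mixed model to DASS depression and the other continuous scores.
2. For MDE status, take baseline out of the outcome vector and fit one prespecified model to the 1-, 3- and 6-month data: a likelihood-based logistic mixed model with condition, categorical time, condition x time, site and baseline DASS depression score. This keeps the likelihood-based handling of missing follow-up that the article wants.
3. If GEE is preferred, pair it with multiple imputation or weighting, because unweighted GEE needs stronger missing-data assumptions. The two are not interchangeable: a logistic mixed model gives a conditional odds ratio, GEE a marginal one.
4. Make the 3-month contrast primary. Report an odds ratio, stating whether it is conditional or marginal, and a marginal risk difference, each with a 95% CI.

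The cost is wording and slightly more analysis work; no change to data collection is needed. An odds ratio is less direct to read, which is why the risk difference goes beside it.
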